## Abstract

**Background:**

The Dutch flagship project Next Generation ImmunoDermatology (NGID) aims to profile five chronic immune‐mediated inflammatory skin diseases: atopic dermatitis (AD), plaque psoriasis (PSO), hidradenitis suppurativa (HS), chronic spontaneous urticaria (CSU) and cutaneous lupus erythematosus (CLE) in comparison with cutaneous T‐cell lymphoma subtype mycosis fungoides (MF) and healthy volunteers. Within NGID, a clinical study entitled: ‘SKIN disease profiling by an Exploratory, pRospective, biomarker study in dermatoloGY practice (SKINERGY)’ will be conducted as a multicentre, parallel‐cohort, open‐label, observational, longitudinal basket study.

**Objectives:**

Objectives include evaluation of disease‐related characteristics in comparison to those of healthy volunteers and evaluation of biomarkers for disease stratification and (targeted) treatment response in patients in a real‐world clinical setting. Additionally, differences and similarities in disease characteristics between diseases, changes over time, and profiles of responders versus non‐responders will be evaluated.

**Methods:**

Patients with AD (*N* = 120), PSO (*N* = 160), HS (*N* = 80), CSU (N = 120) and CLE (N = 120) will be enrolled in groups of *N* ≤ 40 patients per treatment. Matched healthy volunteers (N = 120) and the MF cohort (N = 120) will serve as control groups. Assessments include blood sampling, skin punch biopsies, tape stripping, skin swabs, (multimodal) imaging, tele‐health and patient‐ and physician‐reported outcomes. This manuscript describes the study protocol prior to data collection and its strategic evaluation of multi‐omics profiling. Patient advocacy groups co‐defined the research agenda and contributed to study design and informed consent document development, ensuring alignment with patients' needs and real‐world relevance.

**Results:**

SKINERGY will generate a machine learning‐ready dataset with information about changes in various biomarkers over time, including histology, metabolomics, spatial proteomics, transcriptomics, lipidomics, microbiomics, imaging biomarkers, tele‐health, patient‐reported outcome measures (PROMs) and clinical parameters.

**Conclusions:**

Identified biomarker profiles within SKINERGY may guide targeted treatment selection, enhance targeted therapeutic response in clinical practice and improve understanding of disease pathology in chronic immune‐mediated skin diseases.

Why was the study undertaken?This study aims to address the limited yield of previous biomarker research in chronic immune‐mediated inflammatory skin diseases by taking a comprehensive, real‐world approach. We will investigate how disease‐related characteristics and biomarker profiles differ among patients with these diseases, how they change over time and how they relate to treatment response. Comparisons with patients with MF and healthy volunteers will serve as a reference to better understand disease‐specific patterns.What does this study add?SKINERGY aims to provide real‐world, cross‐disease, longitudinal insights into chronic immune‐mediated inflammatory skin diseases. By integrating multi‐omics profiling, spatial tissue analysis and patient‐ and physician‐reported outcomes across six diseases and healthy controls, the study is expected to identify both shared and disease‐specific mechanisms. Its nationwide, representative design and mechanism‐based patient stratification may generate a harmonized, high‐quality dataset. This dataset will support machine learning approaches for biomarker identification and validation.What are the implications of this study for disease understanding and/or clinical care?The SKINERGY study is designed to advance the understanding of immune‐mediated inflammatory skin diseases. This will be done through repetitive multi‐omics profiling, with a real‐world study design. By linking biomarker profiles to treatment response, disease characteristics and disease endotypes, SKINERGY has the potential to support the development of personalized treatment algorithms in routine dermatological care.

## INTRODUCTION

Immune‐mediated inflammatory skin diseases are highly prevalent, affecting an estimated 20%–25% of the population,^1^ and have a major physical and psychological impact. Patients often experience persistent itch, sleeplessness, low self‐esteem and, ultimately, a critical impact on their participation in society.^2^ The long‐term impact of inflammatory skin disorders is debilitating as direct consequences span from a lifelong negative impact on quality of life (QoL), decreased productivity at work^3^ and psychiatric comorbidities to a high risk of cardiovascular and metabolic complications.^4^, ^5^, ^6^ The significant burden on patients underscores the need for improved dermatological treatments.^6^, ^7^, ^8^, ^9^ Additionally, generic treatment protocols, that is, ‘one size fits all’, with costly targeted drugs, that is, focusing on a single, distinct molecular target, lead to very high and ever‐increasing healthcare costs in dermatology. This highlights the need for more efficient, tailored strategies, as such broad approaches overlook the complexity of disease transitions.^10^

Numerous studies have highlighted the role of deep phenotyping and disease characterization in enhancing personalized healthcare.^11^, ^12^, ^13^, ^14^, ^15^ Researchers have emphasized the promising value of therapeutic matching using patient biopsies prior to initiating targeted treatments.^16^ Additionally, single‐cell profiling with omics techniques offers great potential for deep phenotyping and a more comprehensive understanding of disease characteristics and endotypes.^17^, ^18^, ^19^ Moreover, microbial communities influence immune balance, drive inflammation and contribute to the progression of inflammatory skin diseases.^20^ Implementing these deep phenotyping approaches is crucial for enhancing personalized treatment in immune‐mediated inflammatory skin diseases, with resulting biomarkers serving as indicators of underlying biological and pathogenic processes, as well as treatment responses.

Currently, various international consortia and research groups are gathering clinical data for deep phenotyping purposes using multi‐omics approaches in different cohorts, for example, the ImmUniverse consortium, the Biomarkers in Atopic Dermatitis and Psoriasis project (BIOMAP), the HIPPOCRATES research programme and the Translational Dermatology Initiative.^21^, ^22^, ^23^, ^24^

Our SKIN disease profiling by an Exploratory, pRospective, biomarker study in dermatoloGY practice (SKINERGY) study is embarked on to further investigate disease mechanisms of atopic dermatitis (AD), psoriasis (PSO), hidradenitis suppurativa (HS), chronic spontaneous urticaria (CSU) and cutaneous lupus erythematosus (CLE) in comparison with cutaneous T‐cell lymphoma subtype mycosis fungoides (MF) and healthy volunteers (HV). The main aim of this observational, longitudinal biomarker study in a real‐world daily practice setting is to generate a harmonized, nation‐wide, high‐quality dataset suitable for machine learning. This may enable the identification of discriminative biomarkers for disease monitoring and identification of patterns of (non)‐response to treatment in The Netherlands. Biomarkers identified in this study require subsequent validation to ensure their reliability, in accordance with FDA guidelines.^25^, ^26^, ^27^ The ultimate goal is to evolve dermatological care from a one‐size‐fits‐all approach to personalized treatment. This manuscript describes the study protocol prior to data collection.

## METHODS

### Design and setting

The SKINERGY study is a national, multicentre, parallel‐cohort, open‐label, observational, longitudinal biomarker study in a real‐world daily practice setting with an observation period of 1 year. This study aims to characterize five relevant immune‐mediated inflammatory skin diseases, along with a lymphoproliferative skin disorder (MF) and HV as control cohorts. This study was initiated within the Next Generation ImmunoDermatology project and collaborates with all Dutch University Medical Centers, that is, Leiden University Medical Center (LUMC), University Medical Center Rotterdam (Erasmus MC), University Medical Center Utrecht (UMCU), Amsterdam University Medical Centers (AUMC), Maastricht University Medical Center (MUMC+), University Medical Center Groningen (UMCG), Radboud University Medical Center (RUMC) and the Centre for Human Drug Research (CHDR). In total, 720 patients will be followed for 1 year after the commencement of a real‐world treatment in the healthcare setting. Multimodal parameters will be evaluated pre‐dose (baseline), at month 3 and at month 6 (core study). The study offers optional assessments, which comprise a 12‐month follow‐up visit, supplementary questionnaires and skin punch biopsies. A total of 120 untreated healthy volunteers will be monitored over 3 months as the control group, with multimodal assessments at baseline and month 3.

### Ethical considerations

The study will be conducted in accordance with the following: (i) the principles of the Declaration of Helsinki, (ii) the Medical Research Involving Human Subjects Act (WMO), (iii) the EU's General Data Protection Regulation effective 25 May 2018 and (iv) applicable laws and regulations. All study procedures have been approved by the Medical Ethics Committee METC Leiden Den Haag Delft, the Netherlands (reference P24.100). Amendments to the study protocol will be submitted for review at the Medical Ethics Committee.

### Sample size

This is an exploratory, hypothesis‐generating study, and the sample size is not strictly based on a statistical rationale. The sample size of up to *N* = 120 per disease (PSO *N* = 160, HS *N* = 80) is deemed sufficient to achieve the primary aim of this study, that is, to characterise the disease in‐depth at baseline and monitoring treatment response of patients in daily practice. A total of 120 patients per disease (PSO *N* = 160, HS *N* = 80) will be enrolled, with *N* ≤ 40 patients assigned to each mechanism‐based treatment arm. Given the observational nature of the study, a sample size of N ≤ 40 patients per treatment was chosen to ensure a sufficiently large cohort, allowing for the inclusion of both super‐responders and non‐responders (expected *N* > 6–8 for almost all treatment arms). In addition, this is a longitudinal study to identify and validate biomarkers. If group differences are too small at the selected sample size, preventing statistically significant discrimination between patient subgroups (e.g. responders vs. non‐responders, lesional vs. non‐lesional skin), the biomarker would be deemed unsuitable for clinical implementation. A control group of 120 healthy volunteers will be enrolled.

### Randomization and blinding

Randomization and blinding are not applicable as it is an observational, non‐randomized, open‐label, real‐world study.

### Intervention and treatment

After enrolment in the study, all patients will initiate real‐world therapy as part of standard care according to the discretion of the attending physician. Therefore, these treatments are not considered interventions in the study. The treatment groups per disease are depicted in Figure 1.

**FIGURE 1 jdv70311-fig-0001:**
[figure not shown]
Cohorts and treatment groups for healthy volunteers, and patients with atopic dermatitis (AD), psoriasis (PSO), hidradenitis suppurativa (HS), chronic spontaneous urticaria (CSU), cutaneous lupus erythematodes (CLE) and mycosis fungoides‐type cutaneous T‐cell lymphoma (MF). Abbreviations: cyclosporine A (CsA), Anti‐Interleukin 4/13 (Anti‐IL4/13), Anti‐Janus kinase (Anti‐JAK), Anti‐tumour necrosis factor (Anti‐TNF), Anti‐interleukin 23 (Anti‐IL23), Anti‐interleukin 17 (Anti‐IL17), Anti‐tyrosine kinase 2 (Anti‐TYK2), chlormethine (CHLORM), topical corticosteroids (TCS), psoralen + ultraviolet A / ultraviolet B (PUVA/UV‐B), anti‐immunoglobulin E (Anti‐IgE), Anti‐Bruton's tyrosine kinase (Anti‐BTK), hydroxychloroquine (HCQ), methotrexate (MTX).

### Primary and secondary outcomes

The primary outcomes of this study will be the percentage of patient (non)‐responders (see Appendix S1), with treatment response defined per disease‐specific criteria based on established thresholds for clinical improvement (e.g. EASI, PASI, CLASI‐A, IHS4), as well as change (Δ) in clinical parameters at 3, 6 and 12 months (Table S1), patient‐reported outcome measures, the time to switch to another therapy, skin surface proteomics and lipidomics, skin microbiome, target lesion and non‐lesional imaging and circulating biomarkers in blood.

The secondary outcomes for this study include patient‐reported outcome measures (PROMs) (Table S2), sleep quality, number of steps and heart rate, percentage of therapy failures and dropouts, type, frequency and quantities of used topical therapies, decrease in disease activity, following physician‐reported outcome measures.

Exploratory endpoints include total body photography, target lesion imaging and skin punch biopsies for histology, immunohistochemistry and multi‐omics strategies including transcriptomics (bulk RNA sequencing), metabolomics (spatial metabolomics using MALDI‐MSI and LC–MS, spatial lipidomics) and proteomics (imaging mass cytometry) and microbiome analysis. A substudy of the following technologies will be deployed: optical coherence tomography for skin morphology and epidermal thickness, multispectral imaging for 3D skin morphology, erythema, haemoglobin, melanin levels and laser speckle contrast imaging for microcirculation.

### Multi‐omics strategy

A diverse range of advanced technologies will provide a comprehensive understanding of disease mechanisms in patients with immune‐mediated inflammatory skin diseases (Table S3). Proteomics, lipidomics and microbiome analyses capture molecular and environmental factors influencing disease. Gene expression profiling using RNA sequencing will reveal the transcriptional signatures underlying disease pathogenesis in blood and skin tissue, and blood analytes provide a window into systemic biomarkers. Tissue‐level profiling will be further explored using imaging mass cytometry and spatial transcriptomics, providing a detailed view of cellular interactions and tissue architecture. Additionally, immunohistochemistry will enhance our ability to assess immune responses and tissue changes, which may provide a clearer perspective on disease progression. This integrated multi‐omics approach may not only deepen our understanding of inflammatory skin diseases but may also help us identify novel disease subtypes and lay the foundation for more targeted and personalized therapeutic strategies (Figure 2; Table 2).

**FIGURE 2 jdv70311-fig-0002:**
[figure not shown]
Multi‐omics strategy for deep phenotyping of inflammatory skin diseases, combining blood, skin tissue via biopsies, skin surface assessments via tape‐strips, imaging, patient‐reported outcome measures (PROMs) and wearables. Advanced techniques enable a comprehensive characterization of disease mechanisms and therapeutic responses and play a pivotal role in enabling personalized treatment strategies.

### Data collection, monitoring and data analysis

Data will be entered in Castor Electronic Data Capture (EDC) and monitored by an independent monitor. Questionnaire data collected through electronic patient‐reported outcome tools is automatically stored in the Castor database. Analyses will follow an intention‐to‐treat approach. Per endpoint, descriptive statistics will quantify the response. Repeated measurements will be analysed with a mixed model analysis of variance with fixed factors group (patients and healthy controls) and the interactions and subject, subject by day and subject by time as random factors. Additionally, the contrast between responders and partial‐ or non‐responders will be assessed. The estimated intra‐subject variability over time will be assessed, and within patients, the contrast between lesional and non‐lesional skin and effects of the different treatments will be assessed. The contrast between the patients and the healthy controls will be calculated within the model. Furthermore, contrasts between patient subgroups will be explored. Exploratory and supervised multivariate (multi‐omics) analyses will be performed using multi‐omics factor analysis approaches, with all exploratory inferences treated as non‐confirmatory, while visualization and testing will be performed with high dimensional ANOVA methods. As additional time‐to‐event context, therapy switching is analysed with Kaplan–Meier and log‐rank methods.

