## DISCUSSION

The SKINERGY study is a multicentre, nationwide, parallel‐cohort, open‐label, non‐randomized, observational, longitudinal biomarker study in a real‐world daily practice setting that aims to identify discriminative potential biomarkers for predictivity of treatment response in The Netherlands. This includes evaluating disease‐related (multi‐omics) biomarkers for disease stratification and targeted treatment (non‐)response over time in patients with AD, PSO, HS, CSU and CLE, compared to an MF control group and healthy volunteers. This enables comparison of inflammatory skin diseases to malignant inflammatory processes in the skin. Additionally, exploratory objectives include the identification of skin tissue and imaging biomarkers correlated with disease progression or therapy response and evaluation of patients’ genomic profiles. By identifying these potential biomarkers, we aim to shift from a ‘one‐size‐fits‐all’ approach to personalized medicine plans through a deep phenotyping approach in real‐world practice.^11^, ^16^, ^17^, ^20^

In previous studies, specific blood‐based biomarkers for inflammatory skin diseases have demonstrated to be highly effective in predicting treatment responses and enabling disease stratification. For instance, an association has been observed between pre‐treatment low serum IgE levels (<30 IU/mL) and partial slow, or non‐response to anti‐IgE therapy with omalizumab in patients with CSU.^28^, ^29^, ^30^ This biomarker is now integrated into clinical practice and can be used to counsel patients eligible for omalizumab treatment. Additionally, several biomarkers associated with the auto‐allergic CSU profile and biomarkers related to the autoimmune type IIb profiles of CSU have been identified, providing valuable insights for disease endotyping in CSU patients and therewith treatment stratification.^31^

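### Intention-to-treat is fixed for all analyses of a non-randomised study that tracks switching, and nothing shown says how a switch affects responder status or later biomarker values

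*Protocol article*

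**What the plan says.** The data-analysis section of the protocol article sets one principle for everything that follows: "Analyses will follow an intention‐to‐treat approach". The same paragraph then covers the repeated-measures models, the contrast of responders with partial or non-responders, the effects of the different treatments and the multi-omics analyses. No other analysis principle is named.

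Under Randomization and blinding, "Randomization and blinding are not applicable". Under Intervention and treatment, therapy is started "according to the discretion of the attending physician".

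The primary outcomes include the percentage of responders and non-responders, with "treatment response defined per disease‐specific criteria based on established thresholds for clinical improvement" and details left to Appendix S1. They also include "the time to switch to another therapy". The percentage of therapy failures is a separate secondary outcome. On analysis, "therapy switching is analysed with Kaplan–Meier and log‐rank methods", which the article presents as added context.

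The Discussion says the study "aims to identify discriminative potential biomarkers for predictivity of treatment response".

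**The concern.** Intention-to-treat earns its place by preserving a randomised comparison, and here there is none to preserve. Its practical effect in this study is to attach each patient's later results to the treatment started at baseline, whatever the patient is taking by then. The scientific question is different: which patients respond to a given mechanism of action.

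The two part company when a patient switches, and the study expects switching because it measures it. If responder status is read from the observed score regardless of switch, an index-drug failure who improves on a second drug joins the responders to the first. Values measured after the switch would also enter the treatment-effect and longitudinal biomarker analyses as effects of the first drug.

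The patients moved in this way come from a small group. The Sample size section expects only somewhat more than 6–8 super-responders and non-responders in most arms of up to 40. It adds that a marker which fails to discriminate at this size would be judged unsuitable for clinical use. Label error could therefore lead to a useful marker being dropped.

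**Working it through.** **The plan's own figures.** The cohorts add up as stated: 120 + 160 + 80 + 120 + 120 + 120 = 720 patients. The article gives no power calculation, switch rate or response rate, so there is no stated figure for this point to reproduce. The only anchor is the expected size of the extreme groups: 6/40 = 15% and 8/40 = 20% of an arm.

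**Inputs.**
- From the Sample size section: arm size 40, and 8 (or 6) true non-responders.
- Assumed: a share s = 25–75% of index-drug failures switch before the assessment, and a share q = 30–70% of those respond to the next drug.
- Assumed: a marker with AUC 0.75, normal with equal variances, so d = √2 × Φ⁻¹(0.75) = 1.414 × 0.6745 = 0.954. Test: two-sided 5% t-test.

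**Formulas.** For N true non-responders:
- mislabelled: m = N × s × q
- labelled groups: N − m non-responders and 40 − N + m responders
- diluted difference: d × [1 − m/(40 − N + m)], because the mislabelled patients carry non-responder marker values into the responder group
- power from the noncentral t distribution on 38 degrees of freedom.

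**Results, N = 8.**

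| s, q | m | Labelled non-responders | Apparent response rate | Diluted d | Power |
|---|---|---|---|---|---|
| no mislabelling | 0 | 8.0 | 80.0% | 0.954 | 65% |
| 25%, 30% | 0.6 | 7.4 | 81.5% | 0.936 | 61% |
| 50%, 50% | 2.0 | 6.0 | 85.0% | 0.898 | 51% |
| 75%, 70% | 4.2 | 3.8 | 90.5% | 0.843 | 33% |

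For the middle row: m = 8 × 0.5 × 0.5 = 2, groups of 6 and 34, and d = 0.954 × (1 − 2/34) = 0.898.

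**Results, N = 6.** Power is 56% without mislabelling and 52% to 28% over the same range, with 0.45 to 3.15 patients mislabelled.

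**A different grouping.** The article contrasts responders with partial and non-responders together. Assume 16 of 40 are in that combined group.
- With the same 2 patients mislabelled, the groups are 14 and 26 and d = 0.954 × (1 − 2/26) = 0.881. Power falls from 82% to 74%, a smaller loss than 65% to 51%.
- This holds only while the number mislabelled stays at 2. If s = q = 50% applied to all 16, then m = 4, d = 0.954 × (1 − 4/28) = 0.818, and power falls from 82% to 64%.

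**The case against.** The strongest reply is that intention-to-treat fixes who is analysed and under which starting treatment, not how response is scored after a switch. Counting a switch for lack of effect as non-response is fully compatible with it, and Appendix S1 may say exactly that. This stands. A reader might infer that the plan labels second-drug improvers as responders to the first drug; no sentence in the article says so, and the responder definition sits in an appendix that is not shown.

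Further points that stand:
- Baseline samples are taken before dosing, so a switch cannot affect them. For baseline predictors only the responder label is at risk.
- Failure, switch and improvement must all precede the assessment. That is least likely at month 3, and the month-12 visit is optional.
- Switching is not ignored. Time to switch and therapy failures are both reported.
- The article says its sample size is not strictly based on a statistical rationale, and the figure of more than 6–8 covers super-responders as well. It would be too strong to say that the sample size rests on the non-responders.
- The power figures depend on assumed rates and on an 8 versus 32 split.

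It can also be said that the handling of switchers is detail which an article leaves to the full protocol. That does not dispose of the point. The article does not merely stay silent; it states a blanket rule that suits its own question poorly. Appendix S1 is cited only for the responder percentage, so even a good rule there would not by itself settle the treatment-effect and longitudinal biomarker analyses.

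**Conclusion.** The concern holds in conditional form. The article fixes intention-to-treat for every analysis of a non-randomised study with tracked switching, and nothing shown ties a switch to responder status or to later biomarker values. If observed status is used regardless of switch, index-drug failures who improve on the next drug would be counted as responders to the first, mainly at months 6 and 12, and post-switch values would be credited to the first drug.

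The actual size is unknown. The range of 0.6 to 4.2 mislabelled patients per arm, and of 65% power falling to 61–33%, rests on the assumed switch and second-response rates, 8 non-responders in 40 and a marker with AUC 0.75. The loss is smaller when partial responders are grouped with non-responders and the number mislabelled is unchanged. The documents do not support saying that mislabelling will occur or that the primary response percentage is inflated as a matter of fact. The rule should be changed, but the point does not invalidate the design.

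**What to change.** For the responder analyses and the biomarker analyses tied to an index treatment, replace the blanket intention-to-treat sentence with a rule that covers every index treatment, whether systemic, topical or phototherapy (the Figure 1 legend lists all three kinds). Suggested wording:

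*A patient who switches from, or adds to, the index treatment for lack of effect before an assessment is analysed as a non-responder to the index treatment at that assessment. Values measured after a switch are not attributed to the index treatment. Switches for other reasons are reported separately. An analysis by treatment as started is given as a secondary description.*

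Reconcile this with the response definitions in Appendix S1, so that one rule applies throughout.

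The cost is mainly wording. Time to switch is already an outcome, so switch dates are needed anyway. The reason for each switch or add-on must be classified, and response percentages may come out slightly lower. The ethics statement reports that no patients had been enrolled at submission, so at that point the rule could still be set before any data were seen. It is an analysis label only and sets no clinical rule on when to switch.

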A potential limitation is that small intergroup differences may limit the detection of statistically significant effects, although the cohort was designed to ensure a sufficient number of non‐responders for biomarker qualification. An additional limitation of this study is that participants are permitted to use topical medications for their skin condition, along with other concomitant treatments, which could influence the results. As the study design is non‐randomized, the bias of the treatment guidelines will influence the data, which is a clear limitation. However, despite these limitations, the choice of a real‐world study design is supported by its relevance and applicability to routine clinical practice. In addition, the synergy to concurrent ongoing consortia in other geographic regions is of pivotal importance for robustness, external validity and statistical power. ^21^, ^23^, ^24^, ^43^

In conclusion, the SKINERGY study aims to generate high‐quality, multi‐omics data on changes across various biomarkers. The biomarkers identified in this study have the potential to enable personalized treatment strategies in clinical practice and deepen the understanding of disease pathology in patients with AD, PSO, HS, CSU, CLE and MF. These advancements have the potential to significantly improve therapeutic efficacy and the quality of life for individuals with immune‐mediated inflammatory skin diseases and MF. Ultimately, we strive to overcome the ‘one‐size‐fits‐all’ approach and shift towards 'the right treatment, for the right patient, at the right time’.

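### Time to switch is a primary outcome, but its only named test is a log-rank with no comparison groups or confounder adjustment stated, in a study where physicians choose the treatment

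*Protocol article*

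**What the plan says.** All references are to the protocol article.

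- **Primary and secondary outcomes** lists "the time to switch to another therapy" among the primary outcomes.
- **Data collection, monitoring and data analysis** gives this outcome one sentence, which says that "therapy switching is analysed with" Kaplan–Meier and log-rank methods. The sentence opens with "As additional time‐to‐event context". It does not say which groups are compared, and it names no covariate, stratum, weight or regression model.
- The same section plans, in its text on repeated measurements, to assess how the treatments differ in effect. It also plans contrasts by responder status and between patient subgroups. None of these is tied to the log-rank test.
- **Intervention and treatment** says therapy is started "as part of standard care according to the discretion of the attending physician". **Randomization and blinding** confirms that "Randomization and blinding are not applicable".
- **Discussion** states that "the bias of the treatment guidelines will influence the data" and calls this a limitation. No analytic remedy is named.
- **Sample size** describes the study as exploratory and hypothesis-generating, with at most 40 patients per treatment arm.

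**The concern.** There are two problems. First, the outcome's status is unclear: one section makes it primary and another treats its analysis as supplementary. A reader cannot tell how much weight a switching result is meant to carry.

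Second, a plain log-rank test asks whether switching distributions differ between groups and makes no allowance for who is in them. Here the physician decides who receives which drug. The Participants section admits a broad range of severity and mixes first starts with restarts after washout, so arms of about 40 need not be alike at baseline. If the groups compared are treatments, a difference in switching may reflect the patients rather than the drug. The curves and p-value could then be read as evidence that patients stay on one drug longer than on another.

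**Working it through.** **No design figure to reproduce.** The article gives no significance level, power, hazard ratio, switching rate or event count for this outcome. What follows only illustrates direction and possible size.

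**Inputs from the article:** 40 patients per arm, one year of follow-up, non-randomized treatment.

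**Assumed inputs:** exponential switching times; 25% of lower-risk patients switch within a year; one binary baseline risk factor multiplies the switching hazard by *h*; its prevalence *p* differs between arms; the drug has no effect; two-sided 5% test.

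**Expected switching in an arm.** The lower-risk hazard is −ln(0.75) = 0.288 per year, so the one-year switching proportion is (1 − p) × 0.25 + p × (1 − 0.75^h).

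- *h* = 2.5: 1 − 0.75^2.5 = 0.513. At p = 20%: 0.8 × 0.25 + 0.2 × 0.513 = 0.303. At p = 70%: 0.3 × 0.25 + 0.7 × 0.513 = 0.434. Switching is thus 30% v 43% with no drug effect, or 40 × 0.303 = 12 and 40 × 0.434 = 17 events.
- *h* = 4: 1 − 0.75^4 = 0.684. At p = 70%: 0.075 + 0.7 × 0.684 = 0.554, or 22 events.

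Across the four scenarios in the next table, the expected events are about 12 to 22 per arm.

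**Rejection rate of the unadjusted log-rank test, no drug effect (1,500 simulated trials per scenario):**

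| High-risk share, arm A v B | h = 2.5 | h = 4 |
|---|---|---|
| 30% v 60% | 11% | 22% |
| 20% v 70% | 24% | 52% |

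A Cox model adjusted for the risk factor rejected in 4–5% of trials throughout. A repeat with 2,500 trials per scenario gave 11%, 23%, 23% and 52% for the unadjusted test (30% v 60% then 20% v 70% at h = 2.5, followed by the same two at h = 4). A log-rank test stratified by the factor gave 4.6–6.0%.

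**A second grid with smaller hazard ratios, including balanced arms (4,000 trials per cell):**

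| High-risk share, arm A v B | h = 1.5 | h = 2 | h = 3 |
|---|---|---|---|
| 50% v 50% | 6.0% | 4.6% | 5.0% |
| 40% v 60% | 5.6% | 6.0% | 10.1% |
| 30% v 70% | 6.6% | 11.1% | 22.3% |
| 20% v 80% | 8.6% | 18.5% | 45.2% |

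The stratified log-rank test stayed between 4.6% and 5.9% in every cell. The Monte Carlo standard error at 5% is √(0.05 × 0.95 / 4,000) = 0.34 percentage points, so the smallest excesses cannot be told from the nominal level. The inflation becomes material when both the imbalance and the risk factor are substantial.

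**The case against.** The strongest reply is that the article never says the log-rank test compares treatments. The groups could be diseases, responder classes or biomarker subgroups, and the stated aims concern biomarkers rather than comparative effectiveness. This stands: a reader might infer a treatment comparison, but the text does not assert one. The inference is still plausible, because the cohorts are built from mechanism-based treatment arms and treatment effects are to be assessed elsewhere in the same section. The alternatives are no safer: diseases differ in the drugs used, and responder status is defined after treatment starts.

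Second, this is a condensed article, and stratification or a regression model may be in the full protocol or analysis plan. That also stands, so it cannot be said that the analysis will be unadjusted. But the article chose to name a method, and that method in its plain form does not suit the design it describes.

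Third, a reader might go further and say the test has no valid error rate. That is too strong. The log-rank test addresses whether switching distributions differ, and in the 30% v 43% scenario they do. Rejection is a false positive only if it is read as a drug effect, a claim the article does not make for switching.

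Fourth, the study is exploratory and the selection bias is disclosed. This lowers the seriousness but supplies no adjustment. The non-confirmatory label in the analysis section belongs to the multivariate multi-omics work, not to the switching sentence.

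Finally, every simulated size rests on assumed inputs, and the good performance of the adjusted analyses comes from adjusting for the single true, perfectly measured factor. Real data will be less kind.

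**Conclusion.** The point holds in conditional form and should be corrected; it does not undermine the study. Two things are firm from the text: the outcome is primary in one section and additional context in another, and its only named inferential method states neither groups nor adjustment although treatment is physician-chosen. If the test compares treatments, baseline differences can pass for a drug difference. The size is unknown from the document. Under the assumptions shown, the chance of a nominally significant difference with no drug effect runs from about 6% under mild imbalance to about 50% under strong imbalance with a strong risk factor, against about 5% after adjustment or stratification. The documents do not support the firmer conclusions that an unadjusted treatment comparison is definitely planned, or that the test is invalid for every purpose.

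**What to change.** 1. Reconcile the status of time to switch between the outcomes section and the analysis section.
2. State which groups the log-rank test compares.
3. Make any treatment comparison of time to switch within disease, using a Cox model or a stratified log-rank test with a small pre-specified set: baseline disease score, prior systemic therapy, and new start v restart. Use a propensity score if events are few.
4. Keep the Kaplan–Meier curves as description and label any unadjusted log-rank p-value descriptive.

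The cost is a few sentences and a little analysis, and the article says it was written before data collection. The downsides are somewhat wider intervals and a tight limit on covariates. With roughly 12–22 events per arm under the assumed rates, adding indicators for the eight participating centres would ask too much of the data. Adjustment removes only measured confounding, so the limitation in the Discussion should stay.
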